### Study population

2.6

All the patients will be divided into 2 groups, performing TR (G1) or standard rehabilitation training (G2). TR will be delivered by means of an advanced video-conferencing system, whereas the patient will be provided with low-cost monitoring devices, able to collect data about his/her health status and quality of life (QoL). In both the groups each treatment (either cognitive or motor, or both as per patient functional status) will last about 1 hour a day, 5 days/week, for 12 weeks. Clinical evaluations will be administered blindly, before and after the treatments. Besides the clinical scales, evaluation regarding burden of care and HTA will be administered by Unit 1 and 3 to contribute to study aims. Besides the analysis of patient and caregiver burden, we will perform an observational study to analyze the patient's suitability to cope with a new system of rehabilitative treatment delivery. Two structured telephone interviews will be administered to the patients (when possible) and/or their caregivers, and to all the healthcare professionals involved in the patient management, 1 week after the beginning and at the end of the TR.

Satisfaction with the program and occurrence of any problem or barrier will be assessed. Longitudinal evaluation will compare baseline scores reported at the first interview with the posttreatment scores.

Besides the general HTA assessment, a second observational study will be specifically focused on Local Health Units (LHU) to verify whether and to what extent the different organizational settings in 2 diverse Italian regions (i.e., Sicily and Veneto) may influence TR feasibility and costs. Initial investments for ICT solutions necessary for TR (videoconferencing system, monitoring equipment, Cloud-based storage and processing solutions) and direct healthcare cost associated with stroke and TBI survivorship will be assessed. One-year direct cost of stroke will be estimated using hospital and LHU electronic records and interview responses of poststroke patients/caregivers. Costs will be reported for 1 year poststroke, and modeled over the lifetime poststroke.

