### Trial design

2.1

This is a multicentric observational, rater-blinded, active-controlled, parallel-group pilot study to evaluate that TR is at least noninferior in comparison with the same amount of usual territorial rehabilitative physical treatments (UTRT). This study will be conducted at the Rehabilitative Units of IRCCS Centro Neurolesi, Messina (Unit 1) and of IRCCS Hospital San Camillo, Venice (Unit 2). Unit 3 (University of Messina) will help in Health Technology Assessment (HTA) evaluation and big data management. The study protocol was approved by the Ethical and Research Committee of IRCCS Centro Neurolesi “Bonino-Pulejo,” Messina, Italy (ID: 08/2018). The trial is registered under trial gov. (NCT03709875).

The study purpose will be explained to the participants, and patients’ consent will be obtained before the enrollment by the principle investigator.

The study has been funded by the Italian Ministry of Health: WFR: GR-2016-02361306.

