### Eligibility criteria

2.2

In both the clinical Units, we plan to enroll a total 40 stroke patients (20 for each treatment setting) and 40 TBI patients (20 for each condition) requiring home motor and cognitive rehabilitation.

Inclusion criteria are: age range 18 to 65 years; diagnosis of stroke and TBI (less than 1 year), according to neuroradiological and clinical assessments; availability of a home internet connection; the presence of a Montreal Cognitive assessment ≥16/30; the presence of a skilled caregiver.

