### Randomization of participants

2.5

The enrolled patients will be balanced for pathology and randomized in 2 groups, performing TR (G1) or standard rehabilitation training (G2), respectively, according to a simple randomization scheme generated by a software (www.randomization.com).

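### With one recruiting centre per region, the Sicily–Veneto sub-study can describe differences in TR feasibility and costs but cannot attribute them to Local Health Unit organisation

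*Protocol article*

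**What the plan says.** Section 2.6 (Study population) adds to the general HTA work a further component: "a second observational study will be specifically focused on Local Health Units (LHU"). Its task is that of verifying "whether and to what extent the different organizational settings in 2 diverse Italian regions (i.e., Sicily and Veneto) may influence TR feasibility and costs".

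Section 2.1 (Trial design) gives the sites: "This study will be conducted at the Rehabilitative Units of IRCCS Centro Neurolesi, Messina (Unit 1) and of IRCCS Hospital San Camillo, Venice (Unit 2"). The third unit supports the HTA evaluation and data management and is not named as a recruiting site. Section 2.8 says that remote sessions run between the patient's home and these clinical units, and that UTRT is given at home under the local organisation of the Messina and Venice districts.

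On case mix, section 2.2 states: "In both the clinical Units, we plan to enroll a total 40 stroke patients (20 for each treatment setting) and 40 TBI patients", the latter again 20 per condition. Numbers are split by treatment and not by centre. Section 2.5 says "The enrolled patients will be balanced for pathology and randomized in 2 groups", using "a simple randomization scheme generated by a software". Centre is not named as a balancing factor.

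On cost, section 2.6 covers direct healthcare cost for both stroke and TBI, but the one-year and lifetime estimates are for stroke only.

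**The concern.** The aim is worded as attribution with a size: whether organisation has an influence, and how much. Two regions, each seen through one hospital, do not supply that. If TR proves cheaper or easier to deliver from Venice than from Messina, the cause could be how the LHUs are organised. It could equally be the institute that runs the TR service, its therapists, or the kind of patient it admits and discharges.

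At stake is the conclusion drawn from the sub-study. A difference between two hospitals could be reported as evidence that regional health organisation drives TR cost or feasibility, and could be read as such by those planning services elsewhere. An analysis plan cannot repair this, because the limit lies in the number of centres per region and not in the choice of model.

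**Working it through.** The plan gives no sample size, model or precision for the regional comparison, so there is no figure of its own to reproduce. The 60 per group in section 2.10 concerns the TR versus UTRT comparison.

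**1. Can organisation be separated from centre and staff?**

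Inputs: two regions, one recruiting unit in each (section 2.1); TR delivered from those units (section 2.8). Write the outcome of a TR patient as

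outcome = a + b₁·region + b₂·centre + b₃·staff + g·diagnosis + error.

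With one centre per region, the region, centre and staff columns are identical. The matrix has 5 columns (intercept, region, centre, staff, diagnosis) and rank 3. Only the sum b₁ + b₂ + b₃ can be estimated. More patients add rows but not rank, so this holds at 80 patients, at the 120 implied by section 2.10 (2 × 60), or at any other number. Unmeasured differences in referral or severity between the two centres fall into the same sum.

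**2. Can the stroke/TBI mix be separated?**

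Inputs: 80 patients (section 2.2: 40 + 40). Assumption: 40 per centre. Diagnosis is known for every patient. With r the correlation between region and diagnosis, variance inflation = 1/(1 − r²).

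| Assumed stroke/TBI mix, centre 1 vs centre 2 | r | Rank of [intercept, region, diagnosis] | Variance inflation |
|---|---|---|---|
| 20/20 vs 20/20 | 0 | 3 of 3 | 1.00 |
| 28/12 vs 12/28 | 0.4 | 3 of 3 | 1/(1 − 0.16) = 1.19 |
| 40/0 vs 0/40 | 1 | 2 of 3 | not estimable |

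An imbalance in diagnosis can be adjusted for at little cost unless it is almost total. If it were left unadjusted, a 70:30 versus 30:70 mix and an assumed gap of 0.5 SD between stroke and TBI would shift the regional contrast by (0.7 − 0.3) × 0.5 = 0.20 SD. Both inputs are assumptions. The mix cannot affect the one-year cost, which covers stroke only. It could affect feasibility and the broader stroke and TBI cost.

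**3. What precision would a description have?**

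Assumption: the 40 TR patients (20 stroke + 20 TBI, section 2.2) divide evenly, 20 per centre.

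- TR only, centre against centre: SE = √(2/20) = 0.316 SD. The difference detectable with 80% power at two-sided 0.05 is (1.960 + 0.842) × 0.316 = 0.89 SD.
- Contrast of the two within-centre TR minus UTRT differences, 20 per cell: SE = √(4/20) = 0.447 SD; 95% half-width 1.96 × 0.447 = 0.88 SD.

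**4. Does the within-centre contrast recover the organisational effect?**

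For centre k, let cₖ be what is common to both arms, oₖ the effect of organisation specific to TR, uₖ its effect specific to UTRT, and sₖ the effect of the centre's own TR team.

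- TR minus UTRT in centre k: (cₖ + oₖ + sₖ) − (cₖ + uₖ) = oₖ + sₖ − uₖ.
- Contrast between centres: (o₂ − o₁) + (s₂ − s₁) − (u₂ − u₁).

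The common part cancels, including any organisational effect shared by both arms. The TR-team difference stays, and the effect of organisation on UTRT is subtracted. Since UTRT follows the local organisation (section 2.8), that last term cannot be taken as zero. The contrast answers a different question: TR cost relative to local usual care.

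**The case against.** The strongest reply has four parts.

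- **The component is modest.** It is labelled observational, says only that settings may have an influence, sits in a pilot study, and is not among the objectives in section 1.2. All true, and it makes the point minor. It does not remove it: an observational study may describe, but the stated task is to verify an influence and its extent.
- **Staffing and prices may be part of the organisational setting.** The sub-study focuses on LHUs, and section 2.11 collects HTA data by structured checklists, so it may be an organisational comparison and not a patient-level test. This stands in part: on a broad definition some of the supposed confounders belong to the exposure. But TR is run from the two research institutes, so the institute's own team is not the LHU's organisation, and neither are patients' severity and referral route.
- **Case mix is adjustable.** A reader might infer from the lack of per-centre quotas that stroke/TBI mix is hopelessly confounded with region. The documents do not support that: diagnosis is recorded, and the figures above show it is separable unless nearly all of one diagnosis is at one centre. Section 2.2 could even be read as 40 + 40 in each unit, which would fix the mix, although its reference to a total speaks against this.
- **No faulty analysis is stated.** A reader might infer that a raw regional contrast will be reported and the UTRT arm ignored. Section 2.6 gives no model or comparator, and section 2.11 plans comparative cost analyses. Such details may lie in a fuller document, and their absence from an article is not a finding.

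**Conclusion.** The point holds in a limited form. The aim in section 2.6 asks for the influence of organisational setting. With one recruiting centre per region, that influence is completely aliased with centre and TR staff, and confounded with unmeasured patient differences, whatever the sample size. This follows from the site structure alone and needs no numerical assumption.

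The other figures are only indications of scale. The 0.89 SD detectable difference and the 0.88 SD half-width assume an even split of 20 per centre and arm, which is not guaranteed because section 2.5 names no balancing by centre. The 0.20 SD shift assumes both a mix and a cost gap, and applies only to an unadjusted contrast.

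A reader might also infer that an arm-by-centre contrast would rescue the aim, or that the trial's main result is at risk. Neither is supported. The contrast still has one centre per region and subtracts a control that itself follows local organisation. The randomised TR versus UTRT comparison does not depend on the regional one. This is a minor point about a secondary aim.

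**What to change.** Change the aim in section 2.6. Suggested wording: *The LHU sub-study will describe the feasibility and costs of TR at the Messina and Venice centres. Results will be reported by centre and by pathology with 95% confidence intervals. Differences between the centres will not be attributed to LHU organisation.*

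As a supplement, the TR minus UTRT cost difference within each centre may be shown alongside. A note should say that UTRT also follows local organisation, so that comparing the two differences concerns TR cost relative to local usual care and is not an organisational effect either.

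The cost is a more modest claim. No new data are needed. Intervals will be wide: with 40 TR patients spread evenly over two centres and two pathologies there would be 10 per cell, and a cell mean would have a 95% half-width of about 1.96/√10 = 0.62 SD. Keeping the attribution aim would instead require several centres in each region, which is a different and larger study.

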### Clinical evaluation

2.7

Neurological examination will be performed by 2 skilled physicians, blindly administering the following Clinical scales: Barthel Index (BI),^[3]^ WHO Disability Assessment schedule (WHODAS-12),^[4]^ Modified Ashworth Scale,^[5]^ Fugl-Meyer,^[6]^ and Tinetti^[7]^ scales. Cognitive status will be evaluated by means of Montreal Cognitive assessment (MoCA),^[8]^ and Frontal Assessment Battery.^[9]^ Beck Depression Inventory (BDI),^[10]^ Coping orientation^[11]^ to problem experienced, Psychological General Well-being Index,^[12]^ and Short-Form-36^[13]^ health outcome will be also blindly administered by a skilled psychologist to evaluate the rehabilitative training-related psychological impact. Finally, Perceived Disease Impact Scale (PDIS)^[14]^ and system usability scale, as well as Caregiver Burden Inventory (CBI),^[15]^ will be also administered to either the patients or caregivers. Besides the clinical scales, evaluation regarding burden of care and HTA will be administered by Unit 1 and 3 to contribute to study aims.

### Telerehabilitative and standard rehabilitation training treatment and recording systems

2.8

The exercises will be delivered to all patients, following a task-oriented paradigm.

(1)*UTRT rehabilitation*: the patients will receive current care and exercises, adjusted in reason of the clinical needs, as usually. Treatments for motor limbs activity will be focused on functional active-assistive and active exercises. Conventional “paper and pencil” training will be used to improve cognitive function.(2)*TR* will be delivered by means of an advanced video-conferencing system, whereas the patient will be provided with low-cost monitoring devices, able to collect data about his/her health status and QoL. All treatments from remote are based on scheduled videoconferences between the patient's home and the Clinical Units, so that the therapist can always control and modify the exercises. A virtual reality based system, consisting of 2 PC-based workstations, located at the patient's home and at the rehabilitation center, will be used. For the motor treatments the patient has to move the real end effector, following the trajectory of the corresponding virtual task displayed on his computer screen. The speech (mainly lexical based) and cognitive (attention focused) exercises will be delivered from the 2 Research Institutes to the patient's home. During the treatment at home, the patients will use wearable monitoring devices to monitor their status (speed, heart rate, respiratory rate, training load, and single-lead ECG in real-time) and to provide real-time feedback during exercises.

The training will be delivered by means of the Virtual Reality Rehabilitation System (VRRS). VRRS represents a real clinical and technological innovation that allows TR, integrating different rehabilitation modules (motor, cognitive, linguistic, and orthopedic). The system let a remote patient monitoring at home, thus reducing the costs of health care and the length of hospital stay. Such tool is conceived as a “central HUB” to which it is possible to connect, through a USB, a series of specific devices, that is, VRRS-Tablet. This latter is given to the patients to perform their exercises at home, under the control of a therapist by means of a hub-workstation, called Cockpit (Fig. 1). Patient's activity is controlled remotely from a workstation. The VRRS-Tablet contains different exercises, automatically adapted to the patient's performance, thanks to an optimal intensity training for every cognitive and/or motor condition. In fact, each exercise has a customizable setting efficiency. The VRRS-Tablet is equipped with patient and therapist mode: the former allows performing the exercises and monitoring the data produced, whilst the latter allows monitoring the patient's progress through the platform. These data will be stored in Cloud-based systems for further evaluation and statistical purposes (Unit 3). UTRT will be delivered in each patient's home, according to the local organizational system (i.e., Messina and Venice districts). The data coming from both clinical Units will be stored and analyzed at IRCCS for blind statistical analysis of primary outcome, and for HTA.

**Figure 1 F1:**
[figure not shown]
Typical telerehab training by using the work station tele-cockpit. On the right, the VRRS-Tablet (on the top) and the complete home VRRS-TR station (on the bottom).

### Participants timeline

2.9

#### Prescreening visit

2.9.1

Evaluation of inclusion and exclusion criteria. Signature of informed consent.

#### Visit 1 (baseline)

2.9.2

Medical history.

#### Visit 2 (at the end of rehabilitative program)

2.9.3

Neurologic and Neuropsychiatric assessment.

### Sample size

2.10

Based on the pilot samples during study, we calculated a minimal sample size of 60 participants per group in this study, given a power of >80% to detect an interaction in the 2-way repeated measures, an effect size of 0.61, 4 variables, and 2 repeated measurements.

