### Statistical analyses

2.11

The disability level will be the principal outcome, measured by WHODAS-12 (primary outcomes), and upper limp Fugl-Meyer (secondary outcome). The global cognitive status, assessed by MoCA, will be also a primary outcome. According to the data distribution, parametric or nonparametric statistical tests will be used. In particular, the independent Student *t* test or the Mann–Whitney *U* test will be used to compare the 2 groups, whereas the Student *t* test for unpaired samples or the Wilcoxon signed-rank test will be used to compare the data collected at the first evaluation and the end of the treatment (intragroup analysis). Linear correlation between variables will be computed by Pearson's coefficient or nonparametric Spearman's rank correlation coefficient. Statistical significance will be set at bilateral alpha level of 0.05. HTA assessment: Data will be collected by means of structured checklists, harmonized with all the units, to be administered to all involved actors. Any required data pooling, transformation, averaging, statistics and overall data processing will be performed by Unit 1 and 3 for assessing proper HTA indicators. With respect to cost analysis, specific direct, and indirect costs will be retrieved from each experimental study to allow performing Cost-Effectiveness and Cost-Minimization analysis within HTA3, to be possibly compared with corresponding cost analysis within HTA1. TR will be supported by the adoption of advanced ICT systems, necessary to set up videoconferencing between remote therapists and patient at home, monitor patient health status and activities, and store and process data collected during TR sessions. Monitoring systems will be composed by low-cost nonintrusive devices (such as bracelet or others).

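### Sample size (2.10) sets a minimum of 60 per group, but Eligibility criteria (2.2) plans 40 per group, and nothing reconciles the two

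*Protocol article*

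**What the plan says.** Section 2.10 (Sample size): "we calculated a minimal sample size of 60 participants per group in this study, given a power of >80% to detect an interaction". The interaction is that of a two-way repeated-measures analysis, with "an effect size of 0.61, 4 variables, and 2 repeated measurements".

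Section 2.2 (Eligibility criteria): "we plan to enroll a total 40 stroke patients (20 for each treatment setting) and 40 TBI patients (20 for each condition").

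Section 2.5 randomises patients to two groups, telerehabilitation (G1) and standard training (G2). Section 2.11 (Statistical analyses) names a t test or Mann–Whitney test between groups and sets the significance level: "Statistical significance will be set at bilateral alpha level of 0.05". The timetable in section 4.5 has a line for the projected number of patients but prints no number, so it cannot settle which figure applies.

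**The concern.** Two sections of one document give different sizes for the same trial. Section 2.10 presents its figure as a minimum tied to a power claim, and the recruitment plan in section 2.2 falls below that minimum. A reader cannot tell whether recruitment should stop at 80 or at 120, or which number the power statement describes.

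This matters for interpretation. The article expects to show that telerehabilitation is at least non-inferior. If the trial is smaller than its own calculation requires, a non-significant difference is more likely to come from low power, and more easily misread as evidence that the treatments are alike.

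**Working it through.** **Inputs from the article.** Minimum 60 per group, power above 80%, effect size 0.61 (metric not stated), four variables, two repeated measurements (2.10). Two-sided alpha 0.05 (2.11). Planned enrolment 20 stroke + 20 TBI per treatment (2.2). Two groups (2.5).

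**Step 1: the head counts.**
- Required: 60 × 2 = 120.
- Planned: 20 + 20 = 40 per group; 40 × 2 = 80.
- Shortfall: (120 − 80)/120 = one third.
- If group meant pathology, the plan also gives 40 against 60. If it meant each pathology-by-treatment cell, the plan gives 20 against 60.

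**Step 2: can 60 be reproduced from the stated inputs?** With two measurements, a t test on change scores is equivalent to the group-by-time interaction. Taking 0.61 as a standardised difference d, the normal approximation is n per group = 2(z₁₋α/₂ + z₀.₈)²/d².
- Alpha 0.05: 2(1.960 + 0.842)²/0.61² = 42.2, so 43 (44 by the t test). This is not 60. At 60 per group, power would be 91.2% (t test).

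The printed figure therefore does not follow from the plain inputs. Two assumptions that the article does not state do return about 60:
- *Alpha divided by the four variables (0.0125).* 2(2.498 + 0.842)²/0.61² = 59.9, so 60. This holds only by the normal approximation. The t test needs 62, and 60 gives 78.8%.
- *d on the raw-score SD, pre-post correlation 0.3, alpha 0.05.* The change-score SD is √(2(1 − 0.3)) = 1.183, so the effective d is 0.61/1.183 = 0.516. Then n = 59.1, so 60 (t-test power at 60 about 80.0%).

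If 0.61 is Cohen's f, 80% power needs only 5 to 38 patients in total, depending on the number of groups, the correlation and the effect-size convention. On that reading 60 per group could not be a minimum.

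**Step 3: power at 40 per group (t test).**

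| Assumption | Power at 40 per group | Does it return about 60? |
|---|---|---|
| d = 0.61, alpha 0.05 | 76.9% | No (44) |
| d = 0.61, alpha 0.0125 | 57.0% | About (60 normal, 62 t) |
| Raw-score SD, correlation 0.3, alpha 0.05 | 62.4% | Yes |
| Raw-score SD, correlation 0.5, alpha 0.05 | 76.9% (same as row 1, since the change-score SD is then 1) | No (44) |
| Raw-score SD, correlation 0.6, alpha 0.05 | 85.4% | No (35) |

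The correlations and the division of alpha are assumptions of this check. The article gives neither.

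**The case against.** **The enrolment sentence might be meant per unit.** It opens by referring to both clinical units. If it meant 80 patients in each, there would be 160 patients and 80 per arm, which satisfies a minimum of 60. With d = 0.61, power would then be about 97% at alpha 0.05 and 91% at alpha 0.0125. This is the best defence. It is the weaker reading, because the sentence itself calls the 40 stroke patients a total, but it shows why the overall number must be printed.

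**A reader might infer that the trial is certainly underpowered, or that its power is about 57%.** The documents support neither. The 57% rests on a four-way split of alpha that sections 2.10 and 2.11 never mention. With d on the raw-score SD and a correlation of 0.6 or more, power at 40 per group exceeds 80%. On the plain reading the shortfall is only about 3 percentage points. This objection stands as far as the size of the loss is concerned. It does not remove the conflict, because on any assumption that makes 40 sufficient, 60 is not the minimum that section 2.10 says it is.

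**The article is a condensed account of a pilot.** Detail such as the correlation may properly sit in a fuller document, and a pilot need not be powered. But both numbers are printed here and they disagree, and section 2.10 makes the power claim itself.

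**Conclusion.** The point holds as a contradiction between sections 2.2 and 2.10: 40 per group planned against a stated minimum of 60, or 80 against 120 in total. Read naturally, planned enrolment is one third below what the article says it needs for more than 80% power. That conclusion needs no assumption beyond two arms and the reading of 80 as the overall total.

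The loss of power depends on assumptions: about 77% at 40 per group on the plain reading (d = 0.61, two-sided 0.05), about 57% to 62% under the assumptions that return roughly 60, and above 80% under some others that do not return 60. No single figure can be called the trial's power from what is written.

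**What to change.** State one overall number and one per-arm number, identically in sections 2.2 and 2.10, and make clear that the number covers both clinical units together.

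- If 80 patients is the target: delete the 60-per-group minimum and restate the power at 40 per arm, with the effect-size metric and alpha used. For d = 0.61 and two-sided 0.05 that is about 77%.
- If 60 per group was always the target: correct section 2.2 to 120 patients, with the split by pathology to match.

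The first option costs wording only, although the stated power becomes less favourable on the plain reading. The second is also a text correction if 120 was always intended. If the working target has in fact been 80, it means recruiting 40 more patients.
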